## Abstract

**Background:**

The high incidence of intraoperative glucose dysregulations in liver transplantation (LT) is related to the lack of highly orchestrated control of intraoperative blood glucose. Glucose monitoring based on a single arterial blood gas test can only provide a simple glucose profile and is insufficient in monitoring intraoperative glycemic variability (GV), which is not conducive to controlling GV and may have a lag in the management of hyper/hypoglycemia. Continuous glucose monitor (CGM), which has been successfully applied in the management of chronic disease in diabetes, provides more detailed blood glucose records and reflect GV parameters such as coefficient of variation (CV%). However, its effectiveness and accuracy for guiding blood glucose management in major surgeries remains unclear.

**Methods:**

This is a single-center, randomized, controlled, superiority trial. One hundred and eighty patients scheduled for orthotopic LT will be recruited and randomized into two groups. All patients are monitored for intraoperative glucose using CGM combined with arterial blood gas (ABG). In the intervention group (group CG), ABG will be performed when CGM value is < 6.1 mmol/L or > 10.0 mmol/L, or the rate of change of CGM value > 1.67 mmol/(L·min). In the control group (group G), intraoperative ABG tests will be performed every 2 h, and the frequency of ABG tests will be adjusted based on the previous arterial glucose result. Patients in both groups will have their blood glucose adjusted according to arterial glucose values and a uniform protocol. Surgical and other anesthetic management is completed according to standard LT practices.

**Discussion:**

This study intends to investigate the effectiveness of CGM-based intraoperative glucose management and its impact on the prognosis of LT patients by comparing the GV, mean glucose values, and the incidence of hypo/hypoglycemic events guided by the above two glucose monitoring methods.

**Trial registration:**

This study is registered at www.chictr.org.cn on January 4, 2022, under the registration number ChiCTR2200055236.

## Introduction

### Background and rationale {6a}

Maintaining blood glucose levels within a reasonable range is a key target of perioperative blood glucose management. Similar to the glucose control performed in regular diabetic patients, strict perioperative glucose control reduces risk of postoperative hyperglycemia-related adverse events such as cardiovascular events [1], short-term mortality [2], and microvascular complications [3] and reduces the risk of surgical site infections (SSIs) and secondary hospitalization rates [4–9]. However, unlike chronic diabetes management, intraoperative glycemic changes are more complex and dramatic due to various exogenous factors, such as fasting, fluid infusion, and traumatic stimuli [3, 10], which makes intraoperative precise glycemic management more difficult. Recent studies demonstrated that hyperglycemia is one of the common complications in liver transplant recipients in the perioperative period, with an incidence ranging from 6.7 to 94% [11, 12], and 45.9% of recipients develop severe hyperglycemia (> 13.4 mmol/L) in the neohepatic phase [13]. In our previous retrospective study, we observed that the incidence of intraoperative glucose peaks between 7.8 and 13.4 mmol/L during liver transplantation (LT) was 68.6%, and the incidence of peak glucose > 13.4 mmol/L was 24.8%. The high incidence of intraoperative glucose dysregulation suggests an urgent need for orchestrated blood glucose control in these patients.

Recent diabetes management guidelines suggest that a sound glycemic management strategy should focus on three pillars: persistent hyperglycemia, hypoglycemia, and glycemic variability (GV) [14–16]. Previous studies have shown that glucose management measures based on intermittent arterial blood gas monitoring of blood glucose have not adequately reduced hyperglycemia-related complications [17], possibly attributable to (1) poor control of intraoperative hyperglycemia [18–20] and (2) ineffective control of intraoperative GV [21, 22]. GV, defined as the degree of fluctuation of blood glucose levels between peak and trough values, serves as a novel prognostic feature of glucose management that is thought to further reduce the incidence of diabetes-related complications [16]. Depending on the observation time frame, measures of GV can generally be divided into two categories: long-term and short-term [15, 23, 24]. Among them, the coefficient of variation (CV%) is considered to be the most appropriate indicator for assessing intraday GV, and it is also easy to perform and interpret when evaluating intraoperative glucose fluctuations. Higher CV% values indicate worse short-term glycemic control, and CV% > 36% is associated with increased risk of hypoglycemia and/or mortality [25, 26]. Rangasamy et al. [27] consolidated the prognostic values of CV%, as a short-term assessment of GV, in predicting serious adverse events after cardiac surgery (OR = 1.91). Consistently, we recently reported that the incidence of early postoperative graft dysfunction was significantly higher in recipients with intraoperative CV% higher than 28% in LT than in recipients with low CV% (10.8% vs 0%, *P* < 0.01). However, conventional glucose monitoring based on a single arterial blood gas test is time-consuming and labor-intensive, and the measured results represent only the instantaneous concentration at the time of blood collection, thus providing only a simple glucose profile [28]. Therefore, there is an urgent need for viable means of intraoperative GV monitoring and prevention of excessive GV [29].

Continuous glucose monitor (CGM) is a wearable device that automatically detects glucose levels from interstitial fluid or blood every 5 min [30, 31]. Among them, interstitial fluid CGM has been widely used in the chronic disease management of diabetic patients due to the advantages of minimally invasive, stability and less complications [32], and its related products have been approved and marketed by the National Medical Products Administration (NMA) of China. Compared with blood gas examination, CGM provides more detailed blood glucose readings. In addition, CGM evaluates GV parameters such as CV% and has gradually become the gold standard for assessing short-term blood GV in recent years [33, 34]. Given that glucose changes are more drastic under intraoperative stress and there is a different degree of lag in glucose concentration changes in interstitial fluid than in blood, whether CGM based on interstitial fluid can accurately and effectively guide intraoperative glucose management still needs to be validated by high-quality prospective studies.

### Objectives {7}

Therefore, we propose the hypothesis that interstitial fluid-based CGM for intraoperative adjunctive glucose monitoring reduces the coefficient of variation of blood glucose and improves glucose control, which may help improve the prognosis of patients after liver transplantation.

### Trial design {8}

To address the shortcomings of the current glucose monitoring, which lacks continuity and dynamics, and cannot reflect the trend of glucose changes, this study explores the feasibility and effectiveness of continuous glucose monitoring (CGM) in major surgery such as liver transplantation using a prospective randomized, controlled, superiority clinical trial [35]. Furthermore, we will compare the effects of CGM-based and traditional blood glucose management measures on the reduction of intraoperative blood glucose variability in liver transplantation and the improvement of postoperative outcomes (e.g., surgical site infection). The study design is shown in Fig. 1.

**Fig. 1 Fig1:**
[figure not shown]
Study design

## Methods: participants, interventions, and outcomes

### Study setting {9}

This is a single-center, randomized, controlled study, which will be conducted at Beijing Tsinghua Changgung Hospital, China. The study intends to enroll 180 patients who are scheduled for allogeneic orthotopic liver transplantation.

All patients who met the inclusion and exclusion criteria were randomly assigned to the intervention and control groups. Intraoperative glucose monitoring will be performed by CGM combined with arterial blood gas (ABG) in the intervention group (CG group) and by ABG alone in the control group (G group). The effectiveness of CGM- and ABG-based intraoperative glucose management and their impact on the prognosis of LT recipients will be evaluated using GV, mean glucose values, and the incidence of hyperglycemic or hypoglycemic events. The study, approved by the Ethics Committee of Beijing Tsinghua Changgung Hospital (approval number: 21288–0-02), will follow the Declaration of Helsinki (2013 version). The study is registered at www.chictr.org.cn (ChiCTR2200055236).

### Eligibility criteria {10}

#### Inclusion criteria

Age 18 ~ 65 yearsType 2 diabetes or preoperative glycosylated hemoglobin (HbA1C) > 6.5%Scheduled for allogeneic orthotopic liver transplantationASA class II ~ IIISigned written informed consent

#### Exclusion criteria

Diabetes mellitus of any type other than type 2Model for end-stage liver disease (MELD) score ≥ 30Severe preoperative infectionSevere preoperative cardiovascular instability, including unstable angina pectoris, left ventricular ejection fraction < 30%, and malignant arrhythmia.Patient refusal

#### Criteria for removal from the trial

Failure to manage anesthesia or blood glucose in accordance with the study protocolIntraoperative massive blood loss, defined as blood loss exceeding 50% of systemic blood volume within 3 h or blood loss at a rate of > 150 ml/hDeath within 3 months after LTLoss of follow-upVoluntary patient withdrawal from the studyFailure to record study data

### Who will take informed consent? {26a}

The investigator ([name]) will initially screen potential participants based on the surgical schedule and e-case the day before the surgery, then presents the details of the purpose, content, possible benefits, and risks of this study in a separate, undisturbed room, and obtains a signed informed consent.

### Additional consent provisions for collection and use of participant data and biological specimens {26b}

N/A. This trial does not involve collecting biological specimens for storage.

### Interventions

#### Explanation for the choice of comparators {6b}

In this study, blood glucose in the control group will be measured by ABG testing at 2-h intervals, and the monitoring frequency will be adjusted according to the single glucose value, which is the most common way of blood glucose monitoring at present. However, this monitoring method has the disadvantages of not reflecting GV and easily missing the diagnosis of blood glucose disorder. In the intervention group, CGM combined with ABG test will be used for blood glucose monitoring. In brief, ABG test will be performed to verify the blood glucose value when the CGM monitoring value is abnormal (< 7.8 mmol/L or > 10 mmol/L). The blood glucose intervention in both groups will be based on the blood glucose values obtained from ABG test.

### Intervention description {11a}

#### Blood glucose management

Blood glucose monitoring

Intraoperative glucose monitoring is performed in both groups using CGM (Guardian RealTime, Medtronic, USA) in combination with arterial blood gas. A disposable glucose monitoring probe will be placed in the patient's upper arm by the investigator 6 h before surgery and connected to the monitoring system.

In the CG group, intraoperative ABG testing will be performed if the CGM value is < 6.1 mmol/L or > 10.0 mmol/L, or the rate of change of CGM value > 1.67 mmol/(L·min). Blood glucose adjustment will be performed according to the arterial blood glucose value.

In the G group, CGM monitoring results were blinded to patients and investigators. Intraoperative arterial blood gas checks will be performed every 2 h, and blood glucose adjustments will be made based on blood glucose results, and the frequency of blood gas tests will be adjusted as needed. CGM is used to record intraoperative glucose data only.2)Blood glucose management target: The intraoperative blood glucose management target is 7.8 ~ 10 mmol/L in both groups.3)Blood glucose-lowering measures: see Table 1 for the intraoperative glucose management measures for patients in both groups.

**Table 1 Tab1:** Blood glucose intervention

Perioperative target blood glucose: 7.8 ~ 10 mmol/L • If ABG-derived blood glucose > 10 mmol/L measured for the first time, start insulin infusion Insulin dose and mode of administration: • Loading dose: 0.1 U/kg, I.V Maintenance dose: (blood glucose value/5)U/h, infusion			
**Blood glucose (mmol/L)**	**If BG increased from previous measurement**	**BG decreased from prior measurement by ≤ 1.67 mmol/L**	**BG decreased from prior measurement by > 1.67 mmol/L**
**> 13.4**	Increase rate by 3U/h	Increase rate by 3U/h	No change in rate
**11.7 ~ 13.4**	Increase rate by 2U/h	Increase rate by 2U/h	No change in rate
**10.0 ~ 11.7**	Increase rate by 1U/h	Increase rate by 1U/h	No change in rate
**7.8 ~ 10.0**	No change in rate	No change in rate	No change in rate
**6.1 ~ 7.8**	No change in rate	Decrease rate by 50%	Hold insulin infusion
**5.5 ~ 6.1**	• Hold insulin infusion • Check BG every 2 h • Restart infusion if BG > 10 mmol/L		
**3.9 ~ 5.5**	• Hold insulin infusion • Check BG every 30 min until BG > 5.5 mmol/L, resume BG checks every 2 h • Restart infusion at 1/2 the prior infusion rate if BG > 10 mmol/L		
**2.8 ~ 3.9**	• Give 25 mL D50 • Check BG every 30 min until BG ≥ 5.5 mmol/L, resume • BG checks every 2 h		
**≤ 2.8**	• Give 50 mL D50 • Check BG every 15 min until BG ≥ 3.9 mmol/L • When BG ≥ 3.9 mmol/L, check BG every 30 min until BG ≥ 5.5 mmol/L. Give 50 mL D50, followed by a continuous intravenous infusion of D10 • After BG ≥ 5.5 mmol/L, resume BG checks every 2 h • Restart infusion at 1/2 the prior infusion rate if BG > 10 mmol/L		

*BG* blood glucose, *mmol* millimoles, *L* liter, *U* units, *h* hour, *D50* 50% dextrose solution, *D10* 10% dextrose solution, *mL* milliliters

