#### Strategies to improve adherence to interventions {11c}

For the participants in the intervention group, the alarm function of the CGM device will be turned on during LT. The device will continuously alert when the blood glucose value monitored by CGM is < 7.8 mmol/L or > 10.0 mmol/L, or the rate of change is > 1.67 mmol/(L∙min), in order to remind the investigator to reconfirm the blood glucose value using ABG test.

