#### Relevant concomitant care permitted or prohibited during the trial {11d}

A conventional anesthetic management protocol is used intraoperatively. In the absence of clear indications, the control group should avoid two blood glucose monitoring intervals of less than 2 h. ABG testing in the intervention group should be performed only when the blood glucose value monitored by CGM is < 7.8 mmol/L or > 10.0 mmol/L, or the rate of change is > 1.67 mmol/(L- min).

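### The CGM arm's rule for arterial testing has two lower triggers, 6.1 and 7.8 mmol/L, so the experimental intervention has no single definition

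*Protocol article*

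**What the plan says.** The lower CGM trigger for an ABG test in the intervention arm is stated five times in the protocol article.

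- Abstract, Methods: "ABG will be performed when CGM value is < 6.1 mmol/L or > 10.0 mmol/L".
- Intervention description {11a}: "ABG testing will be performed if the CGM value is < 6.1 mmol/L or > 10.0 mmol/L".
- Explanation for the choice of comparators {6b}: an ABG test verifies the value "when the CGM monitoring value is abnormal (< 7.8 mmol/L or > 10 mmol/L".
- Strategies to improve adherence {11c}: "The device will continuously alert when the blood glucose value monitored by CGM is < 7.8 mmol/L or > 10.0 mmol/L".
- Relevant concomitant care {11d}: "ABG testing in the intervention group should be performed only when the blood glucose value monitored by CGM is < 7.8 mmol/L", with the upper limit and the rate trigger as the only other grounds.

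A rate trigger of more than 1.67 mmol/(L·min) appears in all of these except {6b}. The Background describes CGM in general as a device that "automatically detects glucose levels from interstitial fluid or blood every 5 min".

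Insulin and glucose are adjusted on ABG values in both groups. Table 1, declared for both groups, also sets timed re-checks, for example "Check BG every 30 min until BG > 5.5 mmol/L, resume BG checks every 2 h".

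**The concern.** Treatment follows the same table in both arms, so the rule for when to draw an arterial sample is what the trial tests. If that rule has two lower limits, two anaesthetists who each follow the article could deliver different interventions. Any effect on CV% would then be hard to tie to one reproducible rule. The Discussion adds weight to this: it names extra, experience-driven ABG tests as a risk in an unblinded trial and relies on a detailed monitoring protocol to contain that risk.

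Two further parts of the rule also look unsound. The rate trigger seems too coarse for the sampling interval, and the restriction in {11d} seems to clash with the timed re-checks in Table 1.

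**Working it through.** The plan gives no figure of its own to reproduce here. The check sets the statements side by side and then does the arithmetic for the rate trigger.

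**1. Lower trigger**

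| Place | Lower limit (mmol/L) | CGM reading from 6.1 to below 7.8 |
|---|---|---|
| Abstract, Methods | 6.1 | not triggered |
| {11a} | 6.1 | not triggered |
| {6b} | 7.8 | test called for |
| {11c} | 7.8 | device alarms |
| {11d} | 7.8 | test permitted |

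Both 6.1 and 7.8 are row limits in Table 1, so neither is an obvious misprint. The Table 1 row for 6.1 to 7.8 mmol/L leaves the insulin rate alone if glucose rose, halves it after a fall of up to 1.67 mmol/L, and holds the infusion after a larger fall. Whether a sample is drawn in this range therefore bears on treatment.

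**2. Rate trigger**

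Inputs: 1.67 mmol/(L·min) from {11a}; a 5-minute interval from the general description of CGM in the Background; upper limit 10.0 mmol/L; lower limit 6.1 or 7.8 mmol/L.

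- Change needed between consecutive readings: 1.67 × 5 = 8.35 mmol/L.
- Width of the no-test band: 10 − 6.1 = 3.9, or 10 − 7.8 = 2.2 mmol/L.
- Fastest change that stays in band: 3.9 / 5 = 0.78, or 2.2 / 5 = 0.44 mmol/(L·min). Both are below 1.67.
- A grid of consecutive reading pairs from 0.1 to 30 mmol/L in steps of 0.1 found no pair with both readings in band that fires the rate trigger, for either band.
- The rate trigger can fire on an in-band reading only if the previous reading was above 6.1 + 8.35 = 14.45 (or 7.8 + 8.35 = 16.15), or below 10 − 8.35 = 1.65 mmol/L. That previous reading had already met a level trigger.
- Sensitivity to the interval: an in-band change could fire the rule only with readings less than 3.9 / 1.67 ≈ 2.3 minutes apart (6.1 band) or 2.2 / 1.67 ≈ 1.3 minutes apart (7.8 band).

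Table 1 uses the same number, 1.67, as a fall in mmol/L between two measurements, with no time unit.

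**3. Restriction in {11d} against Table 1**

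The 15-minute and 30-minute checks run until glucose reaches 3.9 or 5.5 mmol/L. Both values lie below either candidate trigger, so a CGM that roughly agrees with ABG would still be alarming and {11d} would allow the test. Under the 7.8 limit in {11d}, an ABG value below 5.5 mmol/L lacks a low-value trigger only if CGM reads more than 7.8 − 5.5 = 2.3 mmol/L above it. The clash is therefore confined to two situations:

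- Table 1 resumes 2-hourly checks after recovery, but CGM is back in band.
- ABG is low while CGM reads in band. The Background acknowledges that interstitial glucose lags blood glucose, so this is foreseeable.

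**The case against.** One could reconcile {11a} and {11d} formally: below 6.1 mmol/L a test is required, and from 6.1 to 7.8 it is merely allowed. But {6b} says that a test will be done below 7.8, and the {11c} alarm exists to prompt one, so the article does not describe such a two-tier rule.

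It is also fair to say that randomisation, the CGM-derived primary outcome and the shared ABG-based treatment protocol are untouched. The harm is to the definition and reproducibility of the intervention. A reader might infer that the randomised comparison is invalid; nothing in the article supports that.

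Three other strong readings go too far.

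- A reader might infer that the rate trigger can never act. It can fire on a very large move back into the band, and the article does not state the trial device's sampling interval or how it computes a rate. Nor does the shared 1.67 prove a unit slip: in Table 1 it is a titration quantity, so a slip is possible but unconfirmed.
- A reader might infer that the 6.1 limit leaves the 6.1 to 7.8 row of Table 1 unreachable by a low reading. The trigger acts on CGM and the table on ABG, so measurement error will sometimes lead there. The row would be reached less often.
- A reader might infer that {11d} blocks every re-check after a low value. Most short-interval checks are compatible with it, as shown above.

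**Conclusion.** The contradiction in the lower trigger is established from the text alone: two statements give 6.1 mmol/L, three give 7.8, and nothing in the article resolves them. The disputed range is 1.7 mmol/L wide (7.8 − 6.1), and the no-test band is 3.9 or 2.2 mmol/L depending on the version. How many extra ABG tests one version would produce cannot be computed from the article, because that needs a glucose distribution and a CGM error that it does not give. The effect on CV% is therefore possible but of unknown size.

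The other two points are secondary. That the rate trigger adds essentially nothing to the level triggers is conditional on readings about 5 minutes apart, and fails only at intervals under about 2.3 or 1.3 minutes. The conflict between {11d} and Table 1 is real but limited to the two situations described. The main contradiction needs to be resolved because it concerns the definition of the experimental arm.

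**What to change.** - State one lower CGM trigger, chosen by the investigators, and use it in the abstract, {6b}, {11a}, {11c}, {11d} and the device alarm setting.
- State the trial device's sampling interval, check the unit of the rate trigger against it, and confirm whether the 1.67 in Table 1 is meant to be a separate quantity. Say in {6b} whether the rate trigger applies there too.
- Reconcile the restriction in {11d} with the re-check schedule in Table 1, covering both resumed 2-hourly checks and disagreement between CGM and ABG.
- Trial status gives October 2022 as the expected start of recruitment. If patients have already been treated, record which version of the rule and which alarm setting applied to each.

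The choice of threshold and schedule is a clinical decision for the investigators. The cost is a protocol amendment with ethics approval, a check of the alarm setting and re-training of the anaesthesia team; no extra patients are needed.

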#### Criteria for discontinuing or modifying allocated interventions {11b}

Interventions will be suspended in case of unintended or adverse events, or incomplete information collection that may has negative impact on the acquisition and interpretation of data, or in case of serious protocol deviations and implementation errors. Participating patients may withdraw from the study at any time and for any reason they wish, without consequence.

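### Table 1 prints an order to hold insulin for mild low glucose but not in its two lowest bands (2.8–3.9 and ≤ 2.8 mmol/L)

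*Protocol article*

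**What the plan says.** The table is in the protocol article under Intervention description {11a}, Blood glucose management (Table 1). The Abstract calls the glucose adjustment protocol uniform across the two groups.

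- Row 3.9–5.5 mmol/L stops insulin and sets the rechecks: "Hold insulin infusion • Check BG every 30 min until BG > 5.5 mmol/L, resume BG checks every 2 h". It then gives a restart at half the earlier rate once glucose exceeds 10.
- Row 2.8–3.9 gives dextrose and a recheck schedule only: "Give 25 mL D50 • Check BG every 30 min until BG ≥ 5.5 mmol/L, resume", followed by a return to 2-hourly checks. It contains neither a hold nor a restart rule.
- Row ≤ 2.8 begins "Give 50 mL D50 • Check BG every 15 min until BG ≥ 3.9 mmol/L" and ends "Restart infusion at 1/2 the prior infusion rate if BG > 10 mmol/L". It restarts an infusion that the row has not stopped.
- The infusion is first started above 10 mmol/L at "Maintenance dose: (blood glucose value/5)U/h, infusion".

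The only other text that might stop insulin is the general clause in section {11b}: "Interventions will be suspended in case of unintended or adverse events". Section {22} lists hypoglycemia among treatment-related adverse reactions and treats glucose below 3.0 mmol/L as a serious adverse event.

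**The concern.** An insulin algorithm should be most explicit where insulin is most dangerous. Here the stop order is printed for the milder lows and missing for the deeper ones. The protocol's own limit for severe hypoglycemia, below 3.0 mmol/L, falls inside row 2.8–3.9 and takes in all of row ≤ 2.8, the two rows without a hold.

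Patient safety comes first: someone who follows the table to the letter would give dextrose while insulin keeps running. The second issue is how well the intervention is specified. The same table governs both groups, and the rate of hypoglycemic events is a secondary outcome.

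**Working it through.** **Row by row**

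| Glucose (mmol/L) | Hold printed? | Restart rule printed? |
|---|---|---|
| 6.1–7.8 | only after a fall > 1.67 | none |
| 5.5–6.1 | yes | above 10, rate not given |
| 3.9–5.5 | yes | above 10, half prior rate |
| 2.8–3.9 | no | none |
| ≤ 2.8 | no | above 10, half prior rate |

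**When the gap is reached.** A patient whose previous reading fell in a hold row is already off insulin. The gap opens only when glucose drops from a band with insulin running to below 3.9 between two checks. Over a 2-hour interval the smallest falls are:

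- from 7.8 to 3.9, full rate running: (7.8 − 3.9)/2 = 1.95 mmol/L per hour;
- from 6.1 to 3.9, with the rate already halved at the 6.1–7.8 reading ("Decrease rate by 50" per cent, for a fall of at most 1.67): (6.1 − 3.9)/2 = 1.10 per hour;
- from 7.8 to 2.8: (7.8 − 2.8)/2 = 2.5 per hour.

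**Rates.** First-start rate = glucose/5. At 10.1 mmol/L, just above the start threshold, this is 10.1/5 = 2.02 U/h. At 15 mmol/L, an assumed upper value, it is 15/5 = 3.0 U/h. Table 1 also allows increases of 1–3 U/h, so a titrated infusion could run faster.

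**Insulin given after the low reading, table followed literally**

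| Successive readings | Time still running × rate | Units |
|---|---|---|
| 8.5 → 4.5 | held at once | 0 |
| 8.5 → 3.5 → 4.5 | 0.5 h × 2.02 to 3.0 | 1.01 to 1.50 |
| 8.5 → 3.5 → 3.7 → 4.5 | 1.0 h × 2.02 to 3.0 | 2.02 to 3.00 |
| 8.5 → 7.0 → 3.5 → 4.5 (fall 1.5, halved) | 0.5 h × 1.01 to 1.5 | 0.505 to 0.75 |
| 8.5 → 6.5 → 3.5 (fall 2.0) | already held | 0 |
| 8.5 → 2.6 → 4.0 | 0.25 h × 2.02 to 3.0 | 0.505 to 0.75 |

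On the 3.5 paths with insulin running, it runs alongside 25 mL × 50% = 12.5 g of dextrose.

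**Restart.** The table is applied afresh at each reading. A patient recovering from 3.5 through 3.9–5.5 meets that row's hold and half-rate restart. One who lands at 5.5–6.1 meets a hold and a restart rule without a stated rate. No restart rule is met only when glucose goes from below 3.9 past 6.1 in a single check. From 3.5 that is a rise of at least 6.1 − 3.5 = 2.6 mmol/L in 30 minutes.

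**The case against.** The strongest reply is that the hold is implied. A restart in row ≤ 2.8 means nothing unless insulin was stopped, the rows just above hold it, and no anesthesiologist is likely to leave insulin running at 3.5. Sections {11b} and {22} can also be joined: hypoglycemia is a listed adverse reaction, and adverse events suspend interventions. Earlier checks are not forbidden either, since section {11d} says "In the absence of clear indications, the control group should avoid two blood glucose monitoring intervals of less than 2 h", and in the CGM group the alarms should prompt a blood gas before such depths. Finally, the row 2.8–3.9 text has a stray bullet, so a line may have been lost in layout, and the full protocol's table is not shown.

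Much of this stands. It makes a drafting omission by far the likeliest explanation and keeps the practical effect small. It does not close the gap. The suspension clause sits under a heading about allocated interventions, and what is allocated is the monitoring strategy. It names neither insulin, nor a glucose threshold, nor a restart rate. A layout loss would leave the same table to correct.

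A reader might infer more, in three ways that the document does not support:

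- *That the table orders insulin to continue in severe hypoglycemia.* The rows are silent; they do not say so.
- *That restart after any reading of 2.8–3.9 is undefined.* Most recoveries pass through a row that has a restart rule.
- *That the control group is biased toward hypoglycemia because it is checked less often.* Both groups share the table, no frequency of such falls is given, and the literal reading is unlikely to be followed.

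**Conclusion.** The point holds as an internal inconsistency with a safety consequence. Three bands print a hold (one of them conditionally), and the two lowest print none. On a literal reading, a direct fall from 7.8 or above to 3.5 means about 1.0–1.5 U more insulin before the 30-minute recheck, against 0 U after a fall to 4.5. A second recheck still in the band doubles this to about 2.0–3.0 U.

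These figures rest on first-start rates, an assumed upper starting glucose of 15 mmol/L, an unchecked 2-hour interval with a fall of at least 1.95 mmol/L per hour, and a clinician who does exactly what is printed. A larger figure can be built: readings of 8.5 → 3.5 → 6.5 keep insulin running for 0.5 + 2 = 2.5 h, or 5.05 to 7.50 U. It needs the 2.6 mmol/L rebound in 30 minutes and should be read only as an upper bound. Any effect on hypoglycemia rates or on the coefficient of variation is conditional and cannot be quantified from the protocol. The table should be corrected; the trial's analysis is not in question.

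**What to change.** Make the order to hold the insulin infusion the first instruction in rows 2.8–3.9 and ≤ 2.8 of Table 1.

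For consistency, also copy "Restart infusion at 1/2 the prior infusion rate if BG > 10 mmol/L" into row 2.8–3.9. This second change has effect only when glucose rebounds from below 3.9 past 6.1 in one check, or lands at 5.5–6.1, where the printed restart rule does not specify half rate.

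If the full protocol's table already carries these orders, correct the published table to match.

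The cost is a minor table amendment with ethics notification and brief retraining of the anesthesia team. Sample size, outcomes and analysis do not change.

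### Table 1, row ≤ 2.8 mmol/L: a second 50 mL D50 with continuous D10 is placed after recovery to ≥ 3.9 mmol/L, so the row read literally doses against the rest of the table

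*Protocol article*

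**What the plan says.** The rule is in the protocol article, Intervention description {11a}, Table 1, which applies to both groups. The row for arterial glucose ≤ 2.8 mmol/L runs in this order:

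1. "Give 50 mL D50 • Check BG every 15 min until BG ≥ 3.9 mmol/L".
2. "When BG ≥ 3.9 mmol/L, check BG every 30 min until BG ≥ 5.5 mmol/L".
3. In the same step as printed, as a new sentence: "Give 50 mL D50, followed by a continuous intravenous infusion of D10".
4. "After BG ≥ 5.5 mmol/L, resume BG checks every 2 h • Restart infusion at 1/2 the prior infusion rate if BG > 10 mmol/L".

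The two rows above it read:

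- 2.8 to 3.9 mmol/L: "Give 25 mL D50 • Check BG every 30 min until BG ≥ 5.5 mmol/L", with no D10.
- 3.9 to 5.5 mmol/L: "Hold insulin infusion • Check BG every 30 min until BG > 5.5 mmol/L, resume BG checks every 2 h", with no dextrose of any kind.

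The table's footnote defines D50 and D10 as 50% and 10% dextrose. The target in both groups is 7.8 to 10 mmol/L. Adverse event reporting and harms {22} lists severe hypoglycemia, below 3.0 mmol/L, as a serious adverse event.

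**The concern.** The repeated bolus comes after the patient has improved, not after a failure to improve. Its sentence states no glucose condition. The only condition nearby is the one that opens the step, and that describes recovery to 3.9 mmol/L or more. A rescue rule would be expected to repeat the dose while glucose is still low, and the rest of the table follows that logic: less dextrose as glucose is higher.

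What is at stake is safe and uniform rescue dosing. Every patient in this row is below the 3.0 mmol/L limit in {22}, so the row is used only during an event that the protocol itself calls serious. Two trained staff members could follow it in good faith and give different amounts of dextrose. The abstract promises a uniform protocol for glucose adjustment, and the Discussion relies on a detailed, objective protocol to limit investigator bias in an unblinded trial.

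**Working it through.** The article gives volumes and concentrations but no gram totals, so there is no stated figure to reproduce. The check is dose arithmetic and a comparison of rows.

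**Inputs (all from Table 1 and its footnote).** D50 = 0.50 g/mL. Bolus volumes are 25 mL in row 2.8 to 3.9, and 50 mL, printed twice, in row ≤ 2.8.

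**Formula.** Dextrose (g) = volume (mL) × concentration (g/mL).

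- Row 3.9 to 5.5: no bolus, 0 g.
- Row 2.8 to 3.9: 25 × 0.50 = 12.5 g.
- Row ≤ 2.8, one bolus: 50 × 0.50 = 25 g.
- Row ≤ 2.8, both boluses: 25 + 25 = 50 g.
- Ratio to row 2.8 to 3.9: 25 / 12.5 = 2, or 50 / 12.5 = 4.

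**Possible readings of the repeated sentence.**

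- *Literal, in place.* The sentence belongs to the step that opens at 3.9 mmol/L. The patient gets 25 g at the start and 25 g after recovery, total 50 g. The second dose is given at a glucose for which the table's own row gives 0 g, and it is twice the 12.5 g given to a patient measured lower.
- *A separate step whose bullet mark was lost.* It then has no condition at all. The total is again 50 g, and it still follows the recovery step.
- *Misplaced restatement of the first dose, meant only to introduce D10.* Total 25 g.
- *Dose for non-response.* The total is 25 g in a patient who responds and at least 50 g in one who does not. The condition that separates them is not in the row.

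The bolus total is therefore 25 g or 50 g for the same patient, depending on the reader. The literal reading is the one that conflicts with the adjacent rows.

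**D10.** It starts in the same sentence, so it shares the missing condition. The steps that follow relax checks to every 2 h and restart an infusion above 10 mmol/L. That infusion is taken to be insulin, because high glucose triggers it and row 3.9 to 5.5 uses the same wording for insulin. No D10 rate or stop is printed, so no D10 dose can be computed.

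**The case against.** The strongest defence is that the sentence is not ambiguous. Read where it stands, it gives a sequence: first bolus, recovery to 3.9 mmol/L, second bolus with D10. A patient who has been at 2.8 mmol/L or lower and has only reached 3.9 is still well below target, and more dextrose after a deeper low is a legitimate clinical choice. This stands in part. A deliberate second dose cannot be excluded, and the adjacent rows are written for patients measured at those values. But the text does not say that a deliberate second dose is meant, and as printed it doses a recovering patient more heavily than one with a lower measured glucose. If that is intended, it needs stating.

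A second defence is that the text was read from a PDF and its bullet marks are unreliable; row 2.8 to 3.9 shows one that splits an instruction. That is fair, and it is why the point does not depend on bullet position alone. A shifted mark could detach the sentence from its step, but it would not create a second 50 mL instruction.

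Three stronger readings are tempting, and the documents do not support them.

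- *The trial lets D10 run without limit alongside insulin.* The table prints no stop, but this is a condensed article. Section {31c} says that the full protocol is publicly available, and it is not shown here. Rate, titration and stopping of a rescue infusion may be in it, so their absence is not claimed as an error.
- *The second bolus will push glucose above target.* This needs figures that the article does not give. Assume 50 to 100 kg, a glucose space of 0.15 to 0.25 L/kg (7.5 to 25 L), instant mixing and no clearance. Then 25 g is 126.2 mmol (monohydrate) to 138.8 mmol (anhydrous), and the rise is 126.2 / 25 = 5.0 to 138.8 / 7.5 = 18.5 mmol/L. From 3.9 to 5.5 mmol/L the peak would be 8.9 to 24.0 mmol/L, which spans the 10 mmol/L limit. Overshoot is possible but not shown.
- *The arms are treated differently, or the primary outcome is distorted.* The row is identical in both arms, and no rate is given for glucose ≤ 2.8 mmol/L; it is probably seldom reached. Follow-up checks do differ. In the CG group, "intraoperative ABG testing will be performed if the CGM value is < 6.1 mmol/L or > 10.0 mmol/L". In the G group CGM is blinded, and under {11d} "the control group should avoid two blood glucose monitoring intervals of less than 2 h". But that limit lapses when there is a clear indication, which a recent glucose of 2.8 mmol/L or lower plausibly is, and {11a} allows G-group testing to be adjusted as needed.

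The general safeguards, suspension for adverse events in {11b} and serious-event reporting in {22}, apply to these patients, but they do not say which dose to give.

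**Conclusion.** The point holds as a minor safety and uniform-execution correction. The ≤ 2.8 mmol/L row prints the 50 mL D50 dose twice and places the second, with the D10 start, after recovery to 3.9 mmol/L. Literally followed, that is 25 g more dextrose and 50 g in total, against 12.5 g and 0 g in the two rows above. On the other readings the total is 25 g, or it depends on an unwritten condition.

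The gram figures rest only on the printed volumes and the footnoted concentration. The claim of conflict with the table rests on reading the sentence in its printed place; the claim of an unclear total does not. The D10 stop is a point to confirm against the full protocol, not an established error.

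**What to change.** Correct the one row. Preferred form: after the first 50 mL D50, recheck at 15 minutes; only if glucose is still < 3.9 mmol/L, repeat 50 mL D50 and start D10; once glucose is ≥ 3.9 mmol/L, give no further bolus and move to 30-minute checks. A patient who responds then gets 25 g, and one still < 3.9 mmol/L at that recheck gets 50 g by a written rule.

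Alternatives: delete the repeated D50 and give D10 its own condition. If a second dose at ≥ 3.9 mmol/L is intended, say so and state when it applies.

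In the same edit, add that D10 is stopped before insulin is restarted above 10 mmol/L, unless the full protocol already says so.

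The cost is one amended table row, notice to the anesthesia staff, and the ethics committee approval that {25} requires for any protocol change. Sample size, comparison and analysis are unaffected.
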